**Composition, roles, and responsibilities of the coordinating center, steering committee, endpoint adjudication committee, data management team, and other individuals or groups overseeing the trial {5d}**	**[name], [name], [name], Department of Gastroenterology, Dayanand Medical College & Hospital, Ludhiana:** Created study protocol manual. Submitted Institutional review board (IRB) application to local IRB. Later distributed copies of IRB-approved protocol and other documents to other study sites for assistance in completing the same process at their sites. Coordinating monthly conference calls and quarterly steering committee meetings. Established data collection process.Consecutive patients diagnosed to have SAH will be then registered by the site medical team onto the trial site via *Trans European Network for clinical trials services (TENALEA),* a web-based registration and randomization system, and randomized into two groups (group A and B) to receive active drug or placebo 1:1. (Explained in detail in Sects. 16 a, b, c) Monitored data collection and submission of data from all sites: The principal means of data collection and storage from participant visits will be Electronic Data Capture (EDC) via the internet using the In Form database. Data is entered into the EDC system by site personnel. (Explained in detail in Sect. 18). Sites typically notified the coordinating center of adverse events. Responsibility for dissemination of results at the end of data collection and analysis. **Steering Committee:**Composed of the 5 Principal Investigators -[name], [name], [name], [name], [name] • To support and monitor every aspect of the research project. • Make decisions necessary for a fair conduct of the study • Resolve Issues arising out of conduct of the study • Get Status Updates on the conduct of the trial • Encourage the project personnel to ensure a timely, fair and complete study **Endpoint adjudication committee:** Composed of the 5 Principal Investigators of this study—[name], [name], [name],[name], [name]^.^ **This committee monitors** ^The hard endpoints for a patient involved in this study:^ Mortality at 3 months, 1 month • Change in mDF/MELD at 1 month • Change in Endotoxin levels at 1 month • Change in cytokines (alphaTNF,IL6&IL8 levels) at 1 month • Number of episodes of sepsis (pneumonia, SBP, cellulitis, UTI) over 1 month Data management team: Composed of the following -[name], [name], [name],[name], [name], [name], [name] Will record all Primary and Secondary outcome related follow up data, via the Electronic Data Capture (EDC) using the InForm database. (Complete details in Sect. 19

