### Trial design {8}

This is multicenter, parallel, double-blind, randomized (1:1), placebo-controlled trial. This is a superiority trial where the hypotheses is that the treatment intervention (bovine colostrum) is superior to control (placebo) in the treatment of SAH.

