#### Statistical methods

The baseline patients’ characteristics mentioned in Annexure 2 including comorbid-conditions will be compared between the two treatment groups to demonstrate the actual study group balance and to ensure whether a proper randomization is established or not. We will measure central tendency and variability with means and standard deviations or medians and interquartile range for continuous characteristics and frequencies with percentages for categorical characteristics.

For primary outcome “survival at 3 months,” we will first use an unadjusted log-rank test of the Kaplan–Meier survival estimates for the two treatment arms at a two-sided alpha level of 0.05 with survival censored at 3 months. Further, a Cox proportional hazards regression model (with survival censored at 3 months) will be used to estimate the hazards ratio (HR) with 95% confidence interval (CI) associated with treatment arm (A) compared to the reference treatment (B). Parameters which are observed as unbalanced between the groups will be adjusted in the above model. We will also add any potential time-dependent covariates to the model, such as AST and ALT levels at months 1, 2, and 3 to estimate their predictive value for mortality.

Similar unadjusted log-rank test of the Kaplan–Meier survival estimates, and Cox proportional hazards regression model analysis will be planned for secondary outcome survival at 1 month. Other secondary outcomes measures such as change in mDF levels/MELD score, endotoxin levels, and cytokines levels between baseline and 4-week assessment will be assessed for normal distribution by graphical (Q–Q Plot) interpretation and numerical method (Kolmogorov–Smirnov test). A paired *t*-test will be used for all those outcomes which will follow approximately normal distribution and a sign-rank test will be used for skewed parameters. Proportionality assumption will be assessed for the considered ordinal outcome number of episodes of sepsis (pneumonia, SBP, cellulitis, and UTI). Partial proportional odds ratio regression will be used to assess the effect of treatment on the number of episodes of sepsis (pneumonia, SBP, cellulitis, UTI) over 4 weeks. A proportional partial odds model will be used if the treatment group variable will not meet the proportional odds assumption and will have different effects on different severity levels of sepsis.

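### Change in mDF/MELD, endotoxin and cytokines is analysed only with paired tests against baseline, so no test or estimate of colostrum versus placebo is specified for these secondary outcomes

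*Protocol article*

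**What the plan says.** The article describes the design in Trial design {8} as follows: "This is multicenter, parallel, double-blind, randomized (1:1), placebo-controlled trial". The hypothesis stated there is that "the treatment intervention (bovine colostrum) is superior to control (placebo) in the treatment of SAH".

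Secondary outcome measure (under {12}) lists five items. Three are changes in continuous measures at 1 month: mDF/MELD ("Change in mDF/MELD at 1 month"), endotoxin, and the cytokines TNF-alpha, IL-6 and IL-8. The other two are 1-month survival and the number of sepsis episodes.

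Statistical methods ({20a}) takes up the change outcomes with "Other secondary outcomes measures such as change in mDF levels/MELD score, endotoxin levels, and cytokines levels between baseline and 4-week assessment", sends them through a normality check, and then names the test: "A paired *t*-test will be used for all those outcomes which will follow approximately normal distribution and a sign-rank test" for skewed measures. No further method is given for them.

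The same section does compare the arms for the other outcomes. The primary outcome gets an "unadjusted log-rank test of the Kaplan–Meier survival estimates for the two treatment arms at a two-sided alpha level of 0.05" followed by a Cox hazard ratio of arm A against arm B. One-month survival is treated the same way. For sepsis the text reads "Partial proportional odds ratio regression will be used to assess the effect of treatment on the number of episodes of sepsis".

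**The concern.** The trial asks whether colostrum does better than placebo. A paired t-test or signed-rank test of week 4 against baseline answers a different question: has the average patient changed? Run in each arm, it gives two separate statements about change over time. Run on both arms together, it leaves treatment out. In neither case is there an arm difference or a confidence interval for one.

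This matters because Concomitant care {11d} gives standard care to both arms: nutritional support, and treatment of sepsis, ascites, encephalopathy and other complications where indicated. Scores and biomarkers could therefore move in both arms for reasons unrelated to colostrum, and patients enrolled for high scores may also regress towards the mean. A significant paired test in the colostrum arm, or significance in one arm and not the other, could then be misread as evidence for colostrum. These outcomes carry weight in the article: Background {6a} names change in mDF and MELD as the endpoints beyond mortality that reflect liver function, and the proposed mechanism runs through endotoxin and cytokines.

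**Working it through.** **What each named method compares**

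| Outcome | Method in {20a} | Compares the arms? |
|---|---|---|
| Survival at 3 months | Log-rank, Cox | Yes |
| Survival at 1 month | Log-rank, Cox | Yes |
| Sepsis episodes | Ordinal regression with a treatment effect | Yes |
| Change in mDF/MELD | Paired t or signed-rank | No |
| Change in endotoxin | Paired t or signed-rank | No |
| Change in cytokines | Paired t or signed-rank | No |

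Patients are not matched across arms in a parallel design, so the only pairing available is each patient with their own baseline.

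**Is a between-arm test named elsewhere?** The two-group comparison that opens the section concerns baseline characteristics. The analysis-population text ({20a} and {20c}) sets the populations and a two-sided alpha of 0.05. The missing-data text mentions a difference of means for continuous data, but only to define a tipping point in a sensitivity analysis. None of these supplies the missing test.

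**Size of the possible misreading.** The article gives no figure to reproduce for these outcomes: no SD, no expected change, no number assessed at week 4. Its sample size (79 per group) rests on survival alone. The following inputs are therefore assumptions:

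- n = 55 assessed patients per arm
- SD of change = 6 points
- the same mean change Δ in both arms, so no treatment effect
- normally distributed changes
- alpha 0.05 two-sided (from the article)

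The within-arm paired t-test has noncentrality δ = Δ√n / SD with n − 1 = 54 degrees of freedom and critical value 2.005. Let p be the probability of significance in one arm. The arms are independent, so exactly one arm is significant with probability 2p(1 − p). For Δ = 2: δ = 2 × √55 / 6 = 2.47, p = 0.680, and 2 × 0.680 × 0.320 = 0.435.

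| Common change (points) | δ | Colostrum-arm paired test significant | Exactly one arm significant |
|---|---|---|---|
| 0.5 | 0.62 | 9% | 17% |
| 1 | 1.24 | 23% | 35% |
| 1.5 | 1.85 | 44% | 49% |
| 2 | 2.47 | 68% | 43.5% |
| 3 | 3.71 | 95% | 9% |
| 4 | 4.94 | 99.8% | 0.4% |

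In simulation, a two-sample t-test on the changes rejects in about 5% of trials whatever the common change. Single-arm significance rises steadily with the common change. Discordance between arms peaks near 1.5 points and then falls away.

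**Same check at 79 per arm** (simulation, 10,000 trials, no treatment effect), for a common change of 0.2, 0.3 and 0.5 SD:

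- colostrum-arm paired test significant: 43%, 76%, 99%
- paired test pooled over both arms significant: 71%, 96%, 100%
- exactly one arm significant: 49%, 37%, 1.5%
- two-sample test: about 5% throughout

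**What a between-arm test could detect.** With 80% power the standardised difference is (1.96 + 0.84) × √(2/n): 0.45 SD at 79 per arm, 0.51 SD at 60 and 0.63 SD at 40. The last two numbers of assessed patients are assumed.

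**The case against.** **Secondary outcomes only.** Everything affected is secondary. The primary outcome and the sample size rest on survival, and 1-month survival and sepsis also have between-arm methods. This stands. A reader might infer that the trial's main conclusion is at risk, or that the randomised comparison is lost for its secondary outcomes generally; the article supports neither.

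**No stated decision rule.** A reader might infer that a fall within the colostrum arm would be declared a treatment effect. The article does not say that. It does not say whether the paired tests are run per arm or pooled, or how they would be interpreted. What can be said is that a result could be misread, and that no valid comparison is specified to set against it.

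**Dependence on assumptions.** The percentages come from an SD, a common change and a number assessed that the article does not give. At a common change of 3 or 4 points, discordant arms become rare. This also stands, which is why the range is shown. The defect itself does not depend on these figures.

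**A slip, or a matter for the analysis plan.** The authors may have meant unpaired tests, or may correct this in a separate plan. But the article does not leave the method open. It names two tests, both paired, next to between-arm methods for every other outcome. If it is a slip, the text still needs correcting.

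**Deaths before week 4.** A between-arm test on week-4 values covers only patients who have such a value. With planned 3-month survival of 22% against 42%, that restriction is not trivial, and replacing the paired tests does not remove it. This is fair and is addressed in the fix.

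**Conclusion.** The concern holds for change in mDF/MELD, endotoxin and cytokines, three of the five listed secondary outcomes. As written, their analysis cannot show whether colostrum differs from placebo. This follows from the tests named and the parallel design, without any numerical assumption.

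How misleading the paired results could be does depend on assumptions. Over common changes of 0.5 to 3 points, with 55 assessed per arm and an SD of 6, a colostrum-arm paired test would be significant in 9% to 95% of trials with no treatment effect, against about 5% for a between-arm test.

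**What to change.** In Statistical methods, replace the paired t-test and signed-rank test with a between-arm comparison:

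- Preferably ANCOVA of the week-4 value on treatment arm, with the baseline value as covariate. If the data are clearly skewed, use a Wilcoxon rank-sum test on the changes.
- Report the arm difference with its 95% confidence interval. Show within-arm changes descriptively only.
- State that the comparison is among patients with a week-4 value, and interpret it alongside 1-month mortality.

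Log-transforming endotoxin and cytokines, and no longer letting a normality test choose the analysis, are optional refinements. A plain two-sample test would already cure the error.

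The cost is a short text change, documented before unblinding and sent to the site investigators, their ethics committees and the registry, as item {25} requires. No new data are needed: Investigations already schedules the component laboratory tests at baseline and day 28, and endotoxin and cytokines at baseline and end of treatment.

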### Sample size determination {14}

In a recent Indian study, published in 2014 by Singh et al. [11] the mDf score was 77.4 (range 37–235), MELD score was 27.5 (range 19–41), and the survival rate was 22% at 90 days.

Hence, we calculated the sample size on the basis of the above study.

We consider a 20% increase in survival rate (80% power at 5% alpha) to be clinically meaningful and sufficient to change practice. To detect a 20% increase in survival (from 22 to 42%) in 3 months [the sample size was based on survival at a fixed time point (22% vs 42% at 3 months)], we require 79 patients in each group. Assuming 10% dropouts, the total sample size required for the study is 174.

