### Statistical analysis {20a}

#### Statistical methods

##### Statistical methods for primary and secondary outcomes {20a}

Subject population (S) for analysis

Common sensitivity analyses will be attempted to assess the robustness of the results to protocol deviations. For primary survival (efficacy) analysis, we will use intention to treat analysis, in such a way that all study subjects who are randomized, regardless of adherence to study medication, will be used in the analysis in the treatment arms to which they are originally assigned to at randomization (“as randomized”). Thus, the patient set used for the primary analysis according to the ITT principle is called “full analysis set”.

As a supplementary analysis, we will perform a per-protocol analysis using patients who will achieve at least 80% compliance (without any major protocol violations) with treatment arms. Significance will be assessed using a two-sided alpha level of 0.05.

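### The sepsis-episode analysis makes no allowance for time alive, so at equal daily infection rates it leans against whichever arm survives better

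*Protocol article*

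**What the plan says.** The secondary outcome list in the protocol article (Outcomes {12}) includes "Number of episodes of sepsis (pneumonia, SBP, cellulitis, UTI) over 1 month". The Statistical methods text under {20a} treats this count as ordinal: "Proportionality assumption will be assessed for the considered ordinal outcome number of episodes of sepsis". It then names the analysis: "Partial proportional odds ratio regression will be used to assess the effect of treatment on the number of episodes of sepsis". The next sentence gives the fallback: "A proportional partial odds model will be used if the treatment group variable will not meet the proportional odds assumption". It adds the condition that treatment "will have different effects on different severity levels of sepsis".

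Neither sentence mentions days alive, days followed, an offset or a category for death. The section on missing data plans multiple imputation and a tipping-point analysis. It does not say whether a count cut short by death is missing, kept as observed or scored in some other way.

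**The concern.** A count over a fixed window is comparable between arms only if patients are at risk for similar lengths of time. In severe alcoholic hepatitis many patients die within the window, and the trial is designed to show that colostrum changes how many. An ordinal model of the raw count has no exposure term. If colostrum keeps patients alive, they have more days in which to become infected. The comparison then moves against colostrum even when the daily infection risk is the same in both arms.

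Infection bears on the mechanism set out in the Introduction (gut barrier and endotoxin). A real reduction in infection could therefore be diluted in exactly the case where the primary hypothesis is true.

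There is also a wording fault. The default and the fallback name the same class of model, so the check of proportionality has no visible consequence. The fallback also refers to severity of sepsis, whereas the outcome is a number of episodes.

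**Working it through.** **Inputs from the protocol.** Survival at 90 days is 22% (placebo) and 42% (colostrum), from Sample size determination {14}: "To detect a 20% increase in survival (from 22 to 42%) in 3 months". The same section gives 80% power, 5% alpha, 79 per arm and 174 in total with 10% dropout. The window is 4 weeks, taken as 28 days.

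**Assumptions not in the protocol.** Constant hazard of death; 0.3, 0.6 or 1.0 sepsis episodes per 28 days alive, equal in both arms; infection independent of death.

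**The plan's own figure first.**
- Hazard ratio = ln(0.42)/ln(0.22) = 0.573.
- Freedman's formula, two-sided 5% and 80% power: (1.960 + 0.842)² × (1.573/0.427)² ≈ 106.5, so 107 events.
- 107/(0.78 + 0.58) = 78.7, so 79 per arm. 158 × 1.1 = 173.8, so 174, or 87 per arm.

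The stated size reproduces. The protocol gives no figure for sepsis.

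**Time at risk.**
- Daily hazard: placebo −ln(0.22)/90 = 0.01682; colostrum −ln(0.42)/90 = 0.00964.
- 28-day survival, exp(−28λ): 62% and 76%. So 38% and 24% would die inside the window.
- Mean days alive in the window, (1 − exp(−28λ))/λ: 22.33 and 24.54. The ratio is 24.54/22.33 = 1.10.

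With equal daily infection rates, the expected count is therefore about 10% higher on colostrum. A true rate ratio of 0.85 would appear as 0.85 × 1.10 ≈ 0.93.

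**Odds ratio for any episode.** With daily infection rate m = rate/28, P(at least one) = m/(m + λ) × (1 − exp(−28(m + λ))).

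| Rate per 28 days alive | Colostrum | Placebo | Odds ratio |
|---|---|---|---|
| 0.3 | 22.9% | 20.9% | 1.12 |
| 0.6 | 40.1% | 36.8% | 1.15 |
| 1.0 | 56.6% | 52.4% | 1.19 |

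In 3,000 simulated trials per scenario at 87 per arm, a rank test standing in for the ordinal test rejected in about 7%, 7% and 8% of trials, against a nominal 5%. Episodes divided by days alive gave a rate ratio of about 1.00 in every scenario. With equal survival the odds ratio was 1.00.

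**Sensitivity to early death.** If 28-day survival were 45% versus 75% (an assumed scenario), the odds ratios would be 1.32, 1.38 and 1.48, with rejection rates of 12%, 18% and 27%.

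**Sensitivity to informative death.** Suppose infection and death share a gamma frailty (assumed variance 0.5 or 1.0), with the same 90-day survival and equal infection rates. The ratio of raw counts is then 1.23 or 1.47, and the ratio with time alive as exposure is 1.07 or 1.19. The offset removes much of the distortion but not all of it.

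**The case against.** The strongest reply is that a reader might infer that the plan scores early deaths as infection-free, and it says no such thing. That is right. A patient infected before death contributes the episode: in the base scenario 13% to 34% of placebo patients who die by day 28 have at least one. The missing-data section could also be read as imputing truncated counts. What can be said is narrower: counts are truncated by death, and their handling is not stated.

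A second reply is that offsets and the handling of death belong in the statistical analysis plan, which is not at hand. Silence alone would indeed be no finding. But the protocol does fix the model, and that model as named has no exposure term.

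Third, the size rests on assumed infection rates, constant hazard and independence. In the base case it is modest: at 87 per arm the standard error of the log odds ratio is about 0.30 to 0.37, so the shift is roughly a third to a half of one standard error. This stands.

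Fourth, the two model sentences can be read as one rule in which treatment is held proportional unless it fails the check. That reading is possible. On either reading the fault is one of wording and biases nothing by itself.

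Finally, choosing between a rate model and ranking death worst is partly a choice of estimand, and the offset is not a complete cure. This also stands, which is why the sensitivity analysis is needed.

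**Conclusion.** The concern holds in a limited form. The stated analysis of sepsis episodes ignores time at risk. On the plan's own survival hypothesis it would show about 10% more episodes and an odds ratio for any sepsis of about 1.12 to 1.19 against colostrum when daily infection rates are equal. This rests on constant hazard, 0.3 to 1.0 episodes per 28 days alive, infection independent of death, and observed counts being analysed as they stand. Earlier deaths would enlarge the effect; equal survival would abolish it.

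Two stronger inferences are not supported. The protocol does not state that early deaths count as free of infection. Nor does it give grounds to expect an arm with excess early mortality to profit from the analysis; under its own hypothesis the distortion runs against colostrum.

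The duplicated model class and the reference to severity should be corrected for clarity, but they do not bias the result. The outcome is secondary and the primary survival analysis is unaffected. This is a worthwhile, inexpensive improvement.

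**What to change.** 1. Analyse the number of episodes with a negative binomial model, or a Poisson model with robust standard errors, with log of days alive and followed within 28 days as offset. Report the rate ratio with its 95% confidence interval.
2. Because the offset does not fully correct for informative death, add one sensitivity analysis on an ordinal scale: 0, 1, and 2 or more episodes, with death as the worst category. Use a proportional odds model, relaxed to partial proportional odds only if proportionality fails.
3. Correct the wording so that proportional odds is the default and partial proportional odds the fallback, and replace the reference to severity with episode-count categories.
4. State how deaths within 4 weeks enter this outcome.

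Death dates are already needed for the log-rank test. Onset times are recorded for adverse events ({22} Harms), but the protocol does not say that episode dates are captured for this outcome; the rate model needs only the count and the days alive and followed. The cost is a change of wording and one extra model for a secondary outcome.
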